## Abstract

**Background:**

It is estimated that at least 10% of the population infected with SARS-CoV-2 develop Post COVID Condition, which is characterized by a diverse array of symptoms including dyspnea, fatigue, anxiety, depression, and deterioration in quality of life. The SARS-CoV-2 virus can trigger an excessive immune response, characterized by the release of pro-inflammatory cytokines including IL-6, IL-1, TNFα and reactive oxygen species. Specialized Pro Resolving Mediators (SPMs) (17-HAD, 14-HAD and 18_HEPE) that could be useful in Post COVID Condition modulating the inflammatory response. The objective is to determine the change in quality of life, inflammatory profile, functional capacity and emotional variables in a group taking a nutritional supplement (SPMs) plus a telerehabilitation programme.

**Methods:**

ARACOV-2 study is a double-blind, parallel-group, randomized control trial with two parallel interventions: Nutritional supplement and telerehabilitation vs placebo supplement and telerehabilitation. The primary endpoint will be quality of life (EQ-5L-5D). The intervention will last 12 weeks with a daily intake of omega-3 or placebo and a daily supervised rehabilitation programme using telerehabilitation.

**Discussion:**

This study suggests that SPMs supplementation combined with telerehabilitation may improve inflammation and symptoms like fatigue in Post COVID Condition patients. Both interventions have anti-inflammatory potential, and their combined use could enhance physical and mental health outcomes. This approach offers a promising strategy for managing Post COVID Condition symptoms.

**Trial registration:**

ClinicalTrials.gov NCT06063031

## Introduction

The World Health Organization (WHO) defines Post Covid Condition (PCC) as a syndrome characterized by “a history of probable or confirmed SARS-CoV-2 infection, usually three months from the onset of COVID-19, with symptoms that persist for at least two months and cannot be explained by an alternative diagnosis [1]”. It is estimated that at least 10% of the SARS-CoV-2 infected population develop PCC [2] also known as Long-Covid [3]. PCC shares similarities with other post-viral fatigue syndromes (Epstein-Barr or Cytomegalovirus) [4], such as chronic fatigue syndrome/myalgic encephalomyelitis (CFS/ME) particularly in terms of immune system dysregulation and persistent inflammation [5]. PCC is characterized by a broad spectrum of symptoms including, dyspnea, “brain fog”, anxiety, depression, gastrointestinal changes, and a general deterioration in quality of life [6], with fatigue being one of the major impairments for patients [7]. These symptoms suggest a possible overlap in the underlying pathophysiological mechanisms, particularly involving immune system dysfunction and chronic inflammation. However, the etiopathogenesis of PCC is probably multifactorial. Numerous studies suggest that viral RNA may in multiple organs or reactivate latent viruses such as EBV, which could exacerbate symptoms [5,8]. A crucial element of PCC is the presence of chronic hyperinflammation. The SARS-CoV-2 virus can trigger an exaggerated immune response, characterized by the release of proinflammatory cytokines including IL-6, IL-1, TNFα and reactive oxygen species. Some studies have attempted to detect the presence of T cells and NK lymphocytes in these patients with alterations in TCD4+ cells and TCD8+ cells [9,10].

Considering the inflammatory process, nutritional interventions -particularly those involving resolvins such as those derived from omega-3 fatty acids (EPA/DHA)-, are of interest. Omega-3 fatty acids serve as precursors of specialized pro-resolving mediators (SPMs), which play a critical role in resolving inflammation and restoring immune homeostasis by counteracting pro-inflammatory signaling pathways [11,12]. The specialized nutritional supplement used in this study is derived from fish oil containing standardized levels of SPMs derived from fish oil, that could be useful in PCC [13]. By supplementing SPM-rich formulations, it may be possible to modulate the inflammatory response and improve clinical outcomes in PCC patients [14]. In addition to nutritional intervention, the treatment of these patients should be multimodal, with pulmonary rehabilitation, physical rehabilitation and attention to psychological variables [15]. In fact, the WHO highlights the critical importance of rehabilitation for individuals with PCC, with physiotherapy playing a central role in patient recovery. A cohort study by Vanichkachorn et al [16,17], reported the efficacy of personalized rehabilitation programs in improving the overall condition of PCC patients, drawing parallels with treatment strategies used for CFS/ME. Other studies have also demonstrated the efficacy of tele-rehabilitation physiotherapy programs in enhancing post-COVID and Long COVID patients outcomes [18].

Therefore, the aim of this randomized controlled study will be to analyze the impact of a 12-week nutritional intervention with SPMs, combined with a telerehabilitation program, on the quality of life, pro-inflammatory balance, fatigue, dyspnea, respiratory strength, functional status, and psychosocial aspects in PCC patients, compared with a placebo supplementation with the same telerehabilitation program.

## Materials and methods

### Study design

ARACOV-2 will be a double-blind randomized control trial. This protocol has been designed according to the SPIRIT recommendations, approved by the Ethics Committee of Aragón (reference number: PI22/335), and registered at clinialtrials.gov (NCT06063031). Two parallel interventions will be compared: an experimental group (Nutritional supplement of SPMs and telerehabilitation) (NG) and a control group (placebo supplement and telerehabilitation) (PG). The duration of the study will be 12 months, with a 12-week intervention. Participants in the ARACOV project are actively engaged in the study, with enrollment anticipated to conclude by the end of 2024. Data collection is projected to be achieved by April 2025, paving the way for the obtained of study results in the latter half of 2025 (Fig 1).

### Setting and population

ARACOV-2 is part of a broader multicenter study known as “ARACOV” [19], a cohort designed to characterize patients with Post COVID Conditions (PCC), with people from three health centers of Aragón (Spain). Participants enrolled in ARACOV will be informed about the ARACOV-2 study and will provide with a participant information sheet (PIS) and study contact number. Recruitment will take place by the same research team in three Spanish health centers.

### Eligibility criteria

All potential participants will be informed before and will have to give their written consent to participate in the study. The inclusion criteria will be: 1) Aged 18–70 years; 2) Diagnostic criteria for having had COVID-19; 3) PCC symptoms for more than 12 weeks, from the end of the acute phase; 4) Fatigue >4 points on the Fatigue Severity Scale (FSS); 5) Independent locomotion. The exclusion criteria will be: 1) Neurological disease preventing them from following the program; 2) Respiratory failure: SaO2 < 90% or respiratory rate ≧30; 3) Rheumatic diseases or acute musculoskeletal injuries that contraindicates exercise; 4) Not daily access to the Internet; 5) Unable to follow oral and written instructions in Spanish; 6) Allergies to fish, shellfish, crustaceans or any of the components of the supplement; 7) Patients who have participated in or completed another clinical trial for the treatment of symptoms derived from COVID-19 in the last 4 weeks; 8) To take immunosuppressive drugs, corticosteroids or non-steroidal anti-inflammatory drugs in the last 2 weeks and 9) Being pregnant. The dropout criteria will be: 1) Pregnancy; 2) At the discretion of the researcher for safety reasons, and/or an adverse event; 3) Non-compliance or lack of adherence to the protocol for more than 2 consecutive weeks.

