#### Procedures *during the* treatment period.

At weeks 2, 6, and 10 (±3 days), patients will be contacted by telephone to assess their adherence to the dietary supplement using the MARS-5 test and to monitor safety (Appendix 2 in S2 File). All symptoms reported by patients will be further assessed by a specialist in internal medicine and shall assess the intensity of an AA/unwanted effect and record it in the CCL, based on three intensity and relationship levels: mild, moderate and severe/ probable, possible and unrelated. All detected effects shall be reported to the health personnel for the correct follow-up of the patient. If any patients are identified as non-adherent during these intermediate check-ins, the significance of maintaining adherence will be emphasized to maximize health outcomes. Additionally, patients will receive biweekly calls (at weeks 2, 4, 6, 8, and 10 ± 3 days) to monitor their telerehabilitation treatment, during which the intensity and level of exercises will be reviewed and adjusted as necessary (Fig 2).

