### Intervention

The treatment will take place for 12 weeks and will include both nutritional supplement and telerehabilitation. Participants must complete a therapeutic exercise programme five days a week via HEFORA telerehabilitation platform, which can be accessed at www.hefora.net or through the mobile app (HEFORA, Fisio Consultores, Zaragoza, Spain). The rehabilitation program will be designed following the recommendations of the NICE guideline [21,22] and the European and American Thoracic Societies [22]. It will include aerobics, strength and pulmonary rehabilitation, structured into three levels of difficulty, each featuring different exercises, except for [23] the pulmonary exercises (Appendix 1 in S1 File). Participants will be categorized into levels based on their fatigue measured with the FSS scores: those scoring 6.00 or higher will be in the first level, those with scores between 5.00 and 5.99 in the second, and those scoring between 4.00 and 4.99 in the third. Each participant will begin with 10 minutes of the prescribed aerobic exercises and three sets of strength exercises, performing as many repetitions as they can manage. The pulmonary exercises will remain consistent throughout the intervention, consisting of 2 sets of 10 repetitions each, with a target fatigue level of less than 3 on the Borg Scale.

For the first two weeks, all participants will perform the exercises with a fatigue intensity ranging between 3.00 and 4.00. After two weeks, this intensity will be increased to a range of 5–7. Progression in the exercise program will be assessed every two weeks during control calls. If any symptoms worsen, the participant’s progression in the program will be paused until the next assessment.

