#### Adherence.

Adherence to the telerehabilitation program will be recorded through the mobile application by pressing the “done” button for each exercise in the application itself. It will be coded as follows: 0= if the activity was not done, 1= if they have done some exercises that day, 2 = if they have all exercises that day. Those who complete more than 80% of the sessions (code 1 or 2) will be considered very adherent. “Non-adherent” will be understood as those who completed less than 20% of the sessions [57]. The rest will be considered “partially adherent.”

To evaluate adherence to the supplement, the patient will return the leftover product at last visit and the % adherence will be calculated according to the following formula: % Adherence = (Units taken/ Theoretical units to be taken in x days)*100. Patients will be considered adherent when the percentage adhesion is between 90–100%.

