#### Statistical analysis.

Statistical analysis will be performed with IBM-SPSS Statistics software version 25 or later. Quantitative variables will be described as mean and standard deviation (SD) if the variable follows a normal distribution or as median and interquartile range for non-normal data. For categorical data absolute and relative frequencies will be computed. The Kolmogorov-Smirnov test will be used to determine the normality of the data. Intra-group variables will be measured with the T-Student test for related samples or the paired samples Wilcoxon test for non-parametric alternative. For inter-group comparations non-parametric analysis will be performed when a non-normal distribution is assumed, using the U Mann Whiney test for comparisons between groups and T-Student test for normal data. Dichotomous variables will be analyzed using the chi-square test. A significant level of 95% will be assumed (p <0.05). If there are more than 15% dropouts, an intention-to treat (ITT) analysis will be performed. Effect size will be calculated using Cohen’s d to determine clinical significance: negligible, small, medium and large differences will be reflected in effect sizes of < 0.2, 0.2–0.5, 0.6–0.8 and > 0.8, respectively.

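### Non-compliance for more than two weeks counts as dropout, and ITT is promised only above 15% dropouts, so randomised participants can be left out because of behaviour after randomisation

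*Protocol article*

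**What the plan says.** Five sections of the protocol article bear on this.

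- **Eligibility criteria.** The dropout criteria are pregnancy, the researcher's discretion for safety or an adverse event, and "Non-compliance or lack of adherence to the protocol for more than 2 consecutive weeks". The article does not say whether this means exercise, supplement or both, or how much must be missed within a week.
- **Intervention.** "The treatment will take place for 12 weeks and will include both nutritional supplement and telerehabilitation". The exercise part runs on five days a week: "Participants must complete a therapeutic exercise programme five days a week via HEFORA telerehabilitation platform".
- **Procedures during the treatment period.** Supplement adherence and safety are checked by telephone at weeks 2, 6 and 10. "If any patients are identified as non-adherent during these intermediate check-ins, the significance of maintaining adherence will be emphasized to maximize health outcomes". Withdrawal is not mentioned. Further calls about the exercise programme take place every two weeks, the last at week 10.
- **Adherence.** "Those who complete more than 80% of the sessions (code 1 or 2) will be considered very adherent". Code 1 means that only some of the day's exercises were done. The non-adherent class "will be understood as those who completed less than 20% of the sessions", and everyone between is partially adherent. For the supplement, assessed from product returned at the last visit, "Patients will be considered adherent when the percentage adhesion is between 90–100" per cent.
- **Statistical analysis.** "If there are more than 15% dropouts, an intention-to treat (ITT) analysis will be performed". No analysis population is named for 15% or fewer.

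**The concern.** A lapse in adherence happens after randomisation and may depend on the assigned supplement, on symptoms, or on both. If it turns a participant into a dropout, and dropouts may be left out of the analysis, the groups compared are no longer the groups that were randomised.

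The two rules work together. The first decides who is counted as a dropout. The second uses that count to decide whether an ITT analysis is done at all. Below the threshold, nothing in the article commits the sponsor to analysing these participants, even if their day-84 data exist.

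The article's limitations section already names over-representation of better-adherent patients as a bias at recruitment. This rule could add such selection after randomisation, where randomisation no longer protects the comparison.

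A second problem is consistency. A rule based on a consecutive gap, a classification over the whole programme, and a policy of encouragement at check-ins stand side by side, and nothing says how they relate.

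**Working it through.** **1. The plan's own sample size.** Inputs from Sample size calculation: 30% versus 50% improving, two-sided alpha 0.05, power 0.80, 15% loss. With pooled variance and no continuity correction:

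n = [1.960·√(2·0.40·0.60) + 0.842·√(0.30·0.70 + 0.50·0.50)]² / 0.20² = (1.358 + 0.571)² / 0.04 ≈ 93 per arm.

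93 / (1 − 0.15) = 109.4, rounded up to 110. The stated 110 per arm is reproduced and is not in dispute.

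**2. How many participants the rules touch.**
- 15% of 220 is 33. With up to 33 dropouts (taking the 15% as overall), no ITT analysis is promised.
- The loss allowance runs out at 220 − 2·93 = 34 participants, 17 per arm. The 93 is derived above; the article does not state it.
- Power at 30% versus 50%:

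| Analysed per arm | Loss | Power |
|---|---|---|
| 110 | none | 86.2% |
| 93 | 15% | 80.0% |
| 88 | 20% | 77.8% |
| 82 | 25% | 74.8% |
| 77 | 30% | 72.1% |

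**3. Gap rule against the exercise classes.** Sessions planned: 12 × 5 = 60. Two weeks are 10 sessions, so the shortest longer gap is 11.
- 11 missed: 49/60 = 81.7%, very adherent and possibly a dropout.
- 12 missed: 48/60 = 80.0%, which is not above 80%.
- 15 missed (three weeks): 45/60 = 75.0%, partially adherent.

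For wholly missed sessions, the overlap is therefore the single case of 11. It is wider if non-compliance includes doing only part of the day's exercises (code 1 still counts as completed), or stopping only the supplement (exercise adherence can then be 100%).

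**4. The reverse case.** With k sessions done and evenly spread, the longest gap is (60 − k)/(k + 1), rounded up.
- k = 5: 55/6, so 10.
- k = 11: 49/12, so 5.
- k = 4: 56/5, so 12.

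Someone who completes 5 to 11 sessions (8.3% to 18.3%) is non-adherent but need never have a gap above 10.

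**5. Gap rule against the supplement class.** 4 capsules × 84 days = 336. Missing 15 days leaves 4 × 69 = 276, and 276/336 = 82.1%, below 90%. There is no conflict here.

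**6. Possible bias (illustration; the rates among dropouts are assumed and are not in the article).** Let 30% improve in both arms, so that there is no true effect, and let 15% be dropped per arm. The rate among completers is (0.30 − 0.15·r)/0.85, where r is the improvement rate among those dropped.
- r = 0.30: 30.0%.
- r = 0.10: 0.285/0.85 = 33.5%.
- r = 0: 0.30/0.85 = 35.3%.

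If r is 0.30 under placebo and 0 to 0.10 under the supplement, completers show a false difference of 3.5 to 5.3 points. If r is 0.30 in both arms, there is none. Swapping the arms reverses the sign.

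**The case against.** The strongest reply is that much of the harm is inferred.

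- **Lost data.** A reader might infer that participants dropped for non-compliance have no day-84 data. The article does not say so. It schedules the last visit without excluding anyone, and its ITT clause seems to expect that dropouts can be analysed. What happens to assessments after dropout may be set out in the full protocol. This stands.
- **Loss of poor outcomes.** A reader might infer that the rule removes patients who do badly. Nothing in the article ties lapses to EQ-5D-5L. People may also lapse because they feel better. Both arms follow the same exercise programme under blinding, so lapses in exercise need not differ by arm, and progression is paused if symptoms worsen. This stands for size and direction, but not for the existence of the risk.
- **Flat contradiction.** A reader might say that the dropout rule contradicts the adherence classes. For wholly missed sessions the clash with the top class is one value, the supplement class does not clash, and a withdrawal rule and a descriptive grading serve different purposes. Encouragement at a check-in is also compatible with later dropout; the article does not say that such patients continue. What remains is misalignment around an undefined term.
- **A separate ITT issue.** Much of the consequence does come from the conditional ITT clause. But that clause acts on the dropout count, and the non-compliance rule feeds that count, so the two need to be settled together.

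**Conclusion.** The point holds as a stated rule that risks bias; it is not merely a detail left to a fuller document. The article makes non-compliance for more than two consecutive weeks a dropout criterion and promises ITT only above 15% dropouts. Following it as written allows up to 33 of 220 randomised participants to be left out, including those dropped for non-compliance.

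The size and direction of any bias are unknown. The 3.5 to 5.3 points above rest on assumed differential rates, and equal rates give no bias. Losses under the rule also draw on an allowance of 34 participants, beyond which power at the planned rates falls below 80%. The misalignment with the adherence classes is real but narrow at the top (exactly 11 missed sessions) and wider at the bottom (5 to 11 completed). The stronger claims, that the rule creates outcome-related missing data or that follow-up stops, go beyond what the article says.

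**What to change.** 1. State that meeting the non-compliance criterion is recorded as non-adherence to the intervention and not as withdrawal from the study. Define which component counts and how much must be missed.
2. Seek the day-84 EQ-5D-5L from these participants unless they withdraw consent, at the planned visit or by one added call. The existing calls end at week 10, so the call would be new.
3. Analyse them in their randomised arm whatever the dropout percentage.
4. Reconcile the Eligibility criteria, Procedures during the treatment period, Adherence and Statistical analysis sections.

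Whether the intervention itself continues, and how the pregnancy and safety criteria apply, is left to the sponsor. If data collection has already ended, items 1, 3 and 4 can still be settled before unblinding.

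The cost is a short amendment, a few extra contacts, and possibly a diluted effect estimate. As a pessimistic illustration, if 15% per arm are kept in and all counted as not improved, the planned rates become 25.5% and 42.5% (0.85 × 30% and 0.85 × 50%), and power with 110 per arm is 76.2%. Obtaining their actual outcomes is the way to avoid having to make that assumption.

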### Allocation and blinding

The randomization list will be conducted by the Contract Research Organization (CRO) in a stratified randomization stratified by age and sex using the EPIDAT4 program, a validated system that automates the randomization of treatment arms at the specified ratio, in this case in a 1:1 ratio (NG) or (PG). After baseline the data collection logbook (DCL) will assign a code according to these randomization criteria, which will correspond to the number of the supplementation batch to receive: Nutritional supplement or Placebo.

The treatment will be administered in a double-blind procedure. The allocation list will be kept by specific non-blind personnel from the CRO and the Promoter’s Quality Assurance Department, following good clinical practices. The assessors, the physiotherapist (intervention manager) and other investigators involved in the intervention will be blinded.

### Procedure

Patients who meet the criteria will be scheduled at their participating center. After signing the informed consent (IC) they will carry out the initial assessment.

At the baseline assessment, the nursing team will conduct a series of evaluations. Blood tests will be performed on all participants, and their oxygen saturation and respiratory rate will be measured. Participants will then complete six scales in a single room, a process expected to take approximately 30 minutes. Following this, they will proceed to the physiotherapy assessment, which will begin with the measurement of Maximum Inspiratory and Expiratory Pressure (MIP/MEP). Next, strength tests will be conducted, including the 30-second Arm Curl Test (30“ACT) and the 30-second Sit-to-Stand Test (30”STST). After a 10-minute rest period participants will undergo the 6-Minute Walk Test (6MWT) to assess aerobic capacity. This test will be conducted according to SEPAR guidelines in a 30-meter corridor [20].

In the final phase of the assessment, a physiotherapist will explain the prescribed exercise regimen tailored to each participant’s level and will also install the telerehabilitation mobile application (HEFORA) on the participant’s device.

After randomization by the computer system, the nursing team will provide each participant with a supplement (Nutritional supplement or Placebo). The entire evaluation process will be repeated at the last visit, scheduled for day 84 ± 4, following the same procedures (Fig 2).

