### Outcome measures

#### Primary outcome: Quality of life: EQ-5D-5L.

The EQ-5D-5L is a generic instrument for measuring health-related quality of life that has been validated [23] in Spanish and in PCC patients. It consists of two components: the levels of severity by dimensions and a visual analogue scale (VAS) on general health. The descriptive system contains five dimensions of health (mobility, self-care, activities of daily living, pain/discomfort, and anxiety/depression) and each of them has five levels of severity (From 1=No problem to 5=unable to perform). Participants indicate their perceived overall health on a VAS from 0 (“worst health I can imagine”) to 100 (“best health I can imagine”). The values obtained will be compared with the reference values [24]. Quality of life will be analyzed as a continuous variable by comparing the relevant statistics according to their distribution at the two points in time and as a qualitative variable by comparing the percentage of patients who improve their scores.

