#### Sample size calculation.

To estimate the sample size, a hypothesis test comparing the proportions of independent groups (PG vs. NG) assuming an alpha risk of 0.05 and a beta risk of 0.2 in a bilateral contrast requires 110 subjects in the placebo group and 110 subjects in the Nutritional supplement group to detect the difference in percentage of patients that will improve their EQ-5D-5L after intervention between the two groups, expected to be 30% and 50%, respectively, as statistically significant, and including a 15% loss estimated. Likewise, to assess the improvement in the pro inflammatory balance considering in this case the proportion of patients with change between pre-post intervention balances in each of the groups the estimated sample size will allow a difference of 20% or more between the two to be declared statistically significant, with a confidence level of 95% and a power of 80%. The estimation was carried out using the GRANMO sample size calculator, version 7.12 (Fig 3).

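### EQ-5D-5L is scheduled only at baseline and day 84 ± 4, and no outcome assessment is described for participants who are dropped before that visit

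*Protocol article*

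**What the plan says.** **Measurement schedule.** Under Procedure, the scales are completed at baseline, and then: "The entire evaluation process will be repeated at the last visit, scheduled for day 84 ± 4, following the same procedures". The primary outcome section agrees, since quality of life is to be analysed by "comparing the relevant statistics according to their distribution at the two points in time".

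**Contacts in between.** Under Procedures during the treatment period, at weeks 2, 6 and 10 "patients will be contacted by telephone to assess their adherence to the dietary supplement using the MARS-5 test and to monitor safety". Separately, "patients will receive biweekly calls (at weeks 2, 4, 6, 8, and 10 ± 3 days) to monitor their telerehabilitation treatment". EQ-5D-5L is named at neither set of calls.

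**Leaving before day 84.** Eligibility criteria lists three dropout criteria: pregnancy; the researcher's discretion for safety or an adverse event; and "Non-compliance or lack of adherence to the protocol for more than 2 consecutive weeks". It does not say whether outcomes are still collected afterwards.

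**Analysis and expected loss.** The sample size is given as "including a 15% loss estimated". Under Statistical analysis: "If there are more than 15% dropouts, an intention-to treat (ITT) analysis will be performed". The tests named there are paired t or Wilcoxon, t or Mann-Whitney, and chi-square.

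**The concern.** Each of the named tests needs a day-84 value. For a participant who leaves without that visit, the schedule supplies only the baseline score. An ITT comparison must then assign, model or omit the outcome for that person, with nothing observed after baseline to guide the choice.

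Two of the three dropout criteria, safety or an adverse event and sustained non-adherence, could plausibly be related to how the participant is doing. The article gives no figure for this, but it means the loss cannot be assumed to be random.

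An analysis plan that is not shown may well specify a missing-data method. It cannot recover measurements that were never taken. The point is therefore about data collection. It is separate from the level of dropout at which ITT is triggered and from who counts as a dropout.

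**Working it through.** **Inputs.** From Sample size calculation: 110 per arm, 30% (placebo) against 50% (supplement) improved, two-sided alpha 0.05, power 80%, 15% loss. From Statistical analysis: ITT above 15% dropouts. Equal loss in the two arms is my assumption.

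**1. The plan's own figure.** Two proportions, pooled variance under the null, no continuity correction:

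n = [1.960 × √(2 × 0.40 × 0.60) + 0.842 × √(0.30 × 0.70 + 0.50 × 0.50)]² / 0.20² = [1.358 + 0.571]² / 0.04 ≈ 93 per arm.

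With loss: 93 / 0.85 = 109.4, rounded up to 110. The stated size reproduces.

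**2. How many people the ITT clause concerns.** 15% of 220 is 33, so more than 15% means at least 34 dropouts. All of them lack a post-baseline EQ-5D-5L if none is assessed after leaving.

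**3. How far the data constrain the result.** Let a fraction d be missing in each arm, with 50% and 30% improved among completers.

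- Lower extreme (all supplement leavers fail, all placebo leavers improve): 0.50(1 − d) − [0.30(1 − d) + d] = 0.20 − 1.2d.
- Upper extreme (the reverse): [0.50(1 − d) + d] − 0.30(1 − d) = 0.20 + 0.8d.

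| Missing per arm | Lower | Upper |
|---|---|---|
| 15% | +2 points | +32 points |
| 20% | −4 points | +36 points |
| 30% | −16 points | +44 points |

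At 20%, 22 of 110 per arm are missing. The lower extreme is 40% − 44% and the upper 60% − 24%. The lower bound reaches zero at d = 0.20/1.2 = 16.7%, just above the ITT threshold.

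**4. Two less extreme treatments, at 20% missing.**

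- Completers only: 88 per arm, difference 20 points, power 78%.
- All 110 per arm, missing counted as not improved: 50% × 0.8 = 40% against 30% × 0.8 = 24%, difference 16 points, power 72%.

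**5. What would narrow the bounds.** Only a day-84 value does so directly. A week 6 or week 10 score does not fix day-84 status without a model, does not enter the tests named, and gives nothing for someone who left before that call.

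**The case against.** One post-baseline measurement is a permissible design for a 12-week before-and-after question, and the article states it consistently. Nothing here is an arithmetic error or a contradiction. That stands, and it is why this is an improvement to data collection and not a correction of a mistake.

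A reader might infer that everyone who leaves early is certain to have no outcome, or that the trial has ruled out remote collection. The document supports neither. It does not say that dropped participants are barred from the day-84 visit. It is also a condensed article, and its schedule and design figures and the appendix on the calls are not visible. What can be said is that no assessment after leaving is described, and that the consequence applies to those who leave without the day-84 visit.

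A reader might also take the bounds as a likely error. They are logical extremes that would apply to any trial with that share of missing binary outcomes, and they say nothing about probability. The range of 2 to 32 points belongs to exactly 15% missing, where the ITT clause is not yet triggered; that is why 20% is used for the conclusion.

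Finally, Study design describes recruitment as under way, with enrolment to finish by the end of 2024 and data collection by April 2025. An amendment would reach only part of the sample. That stands as a limit on the benefit.

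**Conclusion.** The point holds as a gap in outcome collection that is cheap to close. Followed as written, the plan gives no post-baseline EQ-5D-5L for anyone who leaves without the day-84 visit, and the ITT analysis kept for the case of 34 or more dropouts would depend on assumptions for them. With 20% missing in each arm, a completer difference of 20 points leaves the difference among all randomised bounded only at −4 to +36 points.

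This rests on the planned 30% and 50% holding among completers, on equal loss by arm, and on no assessment after leaving. Any participant who stops treatment but is still assessed at day 84 falls outside it. The sample size is correct and already allows for the 15% loss.

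**What to change.** 1. State under Eligibility criteria and Procedure that meeting a dropout criterion ends the intervention but not outcome follow-up. The criteria themselves need no change for this.
2. Collect the EQ-5D-5L by telephone or online in the day 84 ± 4 window from every randomised participant who has stopped or cannot attend, and record the mode of administration.
3. Optionally, ask the EQ-5D-5L at the existing week 6 and week 10 calls. This would support a missing-data model but does not by itself narrow the bounds. Day 84 stays the primary time point.

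**Cost.** One amendment and a short questionnaire of five dimensions and a visual analogue scale. Daily internet access is already an entry requirement, the trial app is installed at baseline, and participants are telephoned repeatedly. The drawbacks are mixed modes of administration and coverage only of those still in follow-up when the amendment takes effect. If follow-up has already closed, the point can only inform reporting: give the number without a day-84 value by arm and a sensitivity analysis over assumptions about them.
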